### Therapy combination

Participants who had not previously taken anti-Parkinson medicine (levodopa preparations, dopamine agonists, monoamine oxidase inhibitors, catechins-o-methyl transferase (COMT) inhibitor, anticholinergic drugs, etc.) should postpone the application of Western medicine and take IMPs. Patients who have already received anti-Parkinson treatment should continue to take them on the basis of the original dosage. TCM and proprietary Chinese medicine, except for the prescribed IMPs, are prohibited during the observation period. Reduction of the dosage of anti-Parkinson medication is allowed due to the variations of the disease condition. However, if the symptoms do not improve significantly and they affect the participant’s daily life and the Unified Parkinson's Disease Rating Scale (UPDRS) total score is 3 points higher than at baseline, the only anti-Parkinson medication that can be added is levodopa and benserazide hydrochloride tablets (Madopar, 0.25 g*40 s, Shanghai Roche Pharmaceutical Co., Ltd.); other drugs are prohibited, and the time of adjustment and the current dose should be recorded in detail in the CRF.

Necessary medications for comorbidities must be recorded in the CRF, including the generic name, dosage, and regimen of the drug. Participants will be required to bring all medications they are taking to every follow-up visit to check their concomitant medication.

### Outcomes

Our objectives alternate according to the different stages of PD, so we set different outcomes for each unit for the data analyses. A detailed schedule and list of parameters are shown in Table 2.

**Table 2 Tab2:** Schedule of assessments

Assessments	Group			Study period							O
				Enrolment	Allocation	Intervention				Follow-up	
Timepoint	Mi	Mo	A	−T1	T0	T1	T2	T3	T4	T5	
Enrolment				×							
Eligibility screen	×	×	×	×							
Informed consent	×	×	×	×							
Allocation	×	×	×		×						
Randomization	×	×	×		×						
Intervention											
Ziyin Pingchan formula	×					×	×	×	×		
Jiedu Pingchan formula		×				×	×				
Fuzheng Pingchan formula			×			×	×				
Time of first addition of levodopa	×			×		×	×	×	×	×	P^Mi^
UPDRS	×	×	×	×		×	×	×	×	×	
PDSS-2	×	×		×		×	×	Mi	Mi	×	
ESS	×	×		×		×	×	Mi	Mi	×	
RBDSQ	×	×		×		×	×	Mi	Mi	×	
HAMD	×	×		×		×	×	Mi	Mi	×	
HAMA	×	×		×		×	×	Mi	Mi	×	
SCOPA-AUT	×	×		×		×	×	Mi	Mi	×	
NMSS	×	×	×	×		×	×	Mi	Mi	×	
PDQ-39	×	×	×	×		×	×	Mi	Mi	×	P^A^
Elderly quiver of TCM syndrome classification dysfunction score	×	×	×	×		×	×	Mi	Mi	×	
Duration of “OFF” period		×		×		×	×			×	P^Mo^
Hoehn-Yahr stage		×		×		×	×			×	
WCSS		×		×		×	×			×	
WOQ-9		×		×		×	×			×	
UDysRS		×		×		×	×			×	
AIMS		×		×		×	×			×	
PDYS-26		×		×		×	×			×	
FOGQ		×		×		×	×			×	
CBI			×	×		×	×			×	
MMSE			×	×		×	×			×	
MoCA			×	×		×	×			×	
LED		×		×		×	×			×	
Infection			×	×		×	×			×	
Hospitalization			×	×		×	×			×	
Survival			×	×		×	×			×	
UA	×	×		×		×	×	Mi	Mi	×	
Hcy	×	×		×		×	×	Mi	Mi	×	

*Mi* mild, *Mo* moderate, *A* advanced, *T0* baseline, *T1* week 12, *T2* week 24, *T3* week 36, *T4* week 48, *T * week60, *O* outcome

#### Mild PD

We will use the time of the first addition of levodopa as the primary outcome for the mild PD unit to reveal the progression of the disease. When participants have a 3-point-higher UPDRS III score and have more serious symptoms, their physicians could give them levodopa or increase the dose of levodopa they were taking. The timing will be recorded at every follow-up visit or reported by the participants at any time.

Secondary outcomes will be UPDRS I–IV and total score for disease evaluation, Parkinson’s disease Sleep Scale-2 (PDSS-2), the Epworth Sleeping Scale (ESS), REM sleep behaviour disorder questionnaire (RBDSQ), Hamilton Depression Scale (HAMD), Hamilton Anxiety Scale (HAMA), scales for Outcomes in Parkinson’s disease—Autonomic (SCOPA-AUT), nonmotor symptom scale (NMSS) for assessing NMSs, Parkinson's Disease Questionnaire (PDQ-39) for evaluating QoL, and elderly quiver of TCM syndrome classification dysfunction score for TCM syndrome evaluation, uric acid (UA) and homocysteine (Hcy) for disease prognosis.

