## Methods/design

### Study setting

This study is a multicentre, randomized, double-blind, placebo-controlled clinical trial. The study will be simultaneously carried out in seven centres in China, including Longhua Hospital Affiliated to Shanghai University of Traditional Chinese Medicine, Xinhua Hospital Affiliated to Shanghai Jiao Tong University Medical College, Shuguang Hospital Affiliated to Shanghai University of Traditional Chinese Medicine, No 1 People’s Hospital Affiliated to Shanghai Jiao Tong University Medical College, Yueyang Hospital of Integrated Traditional Chinese and Western Medicine affiliated to Shanghai University of Traditional Chinese Medicine, Ruijin Hospital Affiliated to Shanghai Jiao Tong University Medical College, and Yangzhi Rehabilitation Hospital Affiliated to Tongji University. This study is divided into 3 substudies. PD patients diagnosed at different stages will be screened into different units: mild PD unit, moderate PD unit, and advanced PD unit. The mild PD unit will receive a 48-week therapy and 12-week follow-up, and face-to-face assessments will be conducted at baseline (week 0), week 12, week 24, week 36, week 48, and week 60. The other two units will receive a 24-week therapy and 12-week follow-up, and face-to-face assessments will be conducted at baseline (week 0), week 12, week 24, and week 36. Recruitment for the study will be launched in April 2022 and it is anticipated to finish before July 2024. The flow chart of the trial is shown in Fig. 2.

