### Sample size

The minimum necessary sample size by normal approximation was determined by the following formula [29]:$$n_{1} = n_{2} = 2 \times \left[ {\frac{{\left( {u_{\alpha } + u_{\beta } } \right)\sigma }}{\delta }} \right]^{2} + \frac{1}{4}u_{\alpha }^{2}$$

On the basis of our previous study, the estimated difference in the time of first addition of levodopa between the two groups among mild PD patients was 3.6 months, standard deviation (S.D.) 6.6. The estimated difference in the duration of the “OFF” period between the two groups among moderate PD patients was 4.6 min, S.D. 8.3. The estimated difference in the PDQ-39 score between the two groups among advanced PD patients was 7.3 points, S.D. 8.5. Considering a 5% significance level and a determined 0.10 β value, Uα/2 = 1.96, Uβ = 1.28, we calculated 72 cases are required in each group in the mild PD unit, 84 in the moderate PD unit, and 36 in the advanced PD unit. Considering a 20% drop-out rate, a sample of 172 subjects in the mild PD unit, 168 in the moderate PD unit, and 72 in the advanced PD unit is required, with a total of 412 participants enrolled in the study.

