### Statistical methods

Statistical analysis will be performed using SPSS 25.0 software. Measurement data will be presented as the mean ± S.D. Comparisons between two groups will be conducted using Student’s t-test or the Mann–Whitney U test. Quantitative data will be reported as percentages and proportions, and comparisons between two groups will be performed by χ2 or Fisher’s exact tests. The Mann–Whitney U test will be used to compare the ordinal data. Multivariate analysis will be performed using analysis of variance (ANOVA) or generalized estimation equations (GEE). All analyses will use two-tailed tests with a P value of 0.05 as the threshold for significance.

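### The mild-unit primary outcome is a right-censored time to event, but the protocol gives no rule for participants without the event, lists only complete-data tests and powers the unit as a fully observed mean

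*Protocol article*

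**What the plan says.** The Mild PD section sets the outcome: "We will use the time of the first addition of levodopa as the primary outcome for the mild PD unit". The event depends on a rise in UPDRS III with worse symptoms, after which "their physicians could give them levodopa or increase the dose of levodopa they were taking". Study setting fixes the window: "The mild PD unit will receive a 48-week therapy and 12-week follow-up", that is, 60 weeks. The schedule of assessments collects the outcome through the follow-up visit.

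For the gap between arms, Sample size plans on this: "the time of first addition of levodopa between the two groups among mild PD patients was 3.6 months, standard deviation (S.D.) 6.6". It puts these figures into a formula for comparing two means: "Considering a 5% significance level and a determined 0.10 β value". The result is 72 per group and, after a 20% drop-out allowance, 172 in total.

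Statistical methods says of measurement data: "Comparisons between two groups will be conducted using Student’s t-test or the Mann–Whitney U test". It adds chi-square, Fisher's exact test, ANOVA and GEE, and "All analyses will use two-tailed tests with a P value of 0.05 as the threshold for significance". No survival method appears, and no section says what value a participant without an addition receives.

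**The concern.** A participant who reaches week 60 without adding levodopa, or who leaves earlier, has no observed time. The first kind is the treatment's best result. How these participants enter the comparison decides the estimate and much of the power, and the protocol leaves this open.

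Leaving them out would compare subsets selected after randomisation by the outcome itself. Giving them week 60 would keep them in, but would measure a different and smaller quantity than the 3.6 months used for planning. In either case the planned 90% power belongs to a fully observed variable that this trial will not have. The unit concerned is the largest, 172 of 412 participants.

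**Working it through.** **1. The plan's own figure.** Inputs from Sample size: difference 3.6 months, SD 6.6 months, 1.96 and 1.28.

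n per group = 2 × [(1.96 + 1.28) × 6.6 / 3.6]² + 1.96²/4 = 70.57 + 0.96 = 71.5, rounded up to 72. Then 72 × 1.2 × 2 = 172.8, against 172 stated. The figure reproduces, so the unit was sized as a comparison of two complete means.

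**2. Can the window produce an SD of 6.6 months?** A variable confined to [0, W] has SD at most W/2. If two arms share an SD and their means differ by 3.6, the largest common SD is √[(W/2)² − 1.8²].

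| Window | W (months) | Maximum SD | Maximum common SD with a 3.6-month difference |
|---|---|---|---|
| 48 weeks, calendar months | 11.04 | 5.52 | 5.22 |
| 48 weeks, four-week months | 12 | 6.00 | 5.72 |
| 60 weeks, calendar months | 13.80 | 6.90 | 6.66 |
| 60 weeks, four-week months | 15 | 7.50 | 7.28 |

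At 48 weeks 6.6 is impossible on either scale. At 60 calendar weeks it lies just under the ceiling of 6.66, so nearly everyone would have to add levodopa within days or never. With four-week months the pattern is still extreme: additions in about the first five weeks, or never. The first scheduled UPDRS after baseline is at week 12. For comparison, exponential times cut off at the window have SD of at most 3.98 (48 weeks) or 4.97 (60 weeks).

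**3. What the unstated rule does to power.** The documents give no control mean, so it is varied. Assumptions: Weibull times, SD 6.6 and true difference 3.6 months before censoring, 72 per arm, 60 weeks, no drop-out, two-sided 5%. Simulated values, approximate:

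| Control mean (months) | Difference, adders only (months) | t-test power, adders only | Mann–Whitney power, non-adders tied at week 60 | Log-rank power |
|---|---|---|---|---|
| 9 | 2.0 | 80% | 96% | 91% |
| 12 | 1.4 | 44% | 91% | 88% |
| 15 | 1.0 | 18% | 81% | 80% |
| 18 | 0.65 | 7% | 65% | 63% |

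At control mean 12, 35% of control and 58% of active participants have no observed time. If they are set to week 60, the mean difference is about 1.9 months, not 3.6.

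**4. Log-rank power on an event basis.** The control event proportion p by end of follow-up and the hazard ratio (HR) are assumptions, because the documents give neither. With proportional hazards the active proportion is 1 − (1 − p)^HR. Events D = N × the mean of the two proportions. Power = Φ(½ × √D × |ln HR| − 1.96). With N = 144 (2 × 72 evaluable):

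| HR | p = 30% | p = 50% | p = 70% |
|---|---|---|---|
| 0.5 | 52% | 75% | 88% |
| 0.6 | 33% | 51% | 67% |
| 0.7 | 19% | 30% | 40% |

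Example, HR 0.5 and p = 50%: the active proportion is 29.3%, D = 144 × 0.396 = 57, and Φ(2.62 − 1.96) = 75%. If all 172 were followed to the end, the HR 0.5 row would be 59%, 82% and 93%.

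**The case against.** Four points on the other side deserve weight.

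- **Article and unseen analysis plan.** The methods paragraph is a generic list by data type and ties no test to this outcome. A full protocol or analysis plan may name a survival method. That is fair as to the missing model name alone. But the article does fix the sample size on a complete-data comparison of means, and a later survival analysis would not repair that basis.
- **Mann–Whitney.** A reader might infer that none of the listed tests could serve. The documents do not support that. All mild participants share one 60-week window, so those without an addition can be ranked as tied at the longest time, and the test then performs about as well as log-rank. This stands, with two limits: the protocol states no such rule, and participants lost before week 60 are still not handled. The instruction to contact drop-outs and complete their assessments reduces that loss but does not remove it.
- **Adders-only figures.** A reader might take the 44% as the planned analysis. No section restricts the comparison to participants who added levodopa, so those figures are a worst case.
- **The SD.** A reader might infer that 6.6 months is impossible in this trial altogether. That is proven for 48 weeks only; at 60 weeks it is near-degenerate, not impossible. The figures are attributed to a previous study whose follow-up is not shown, so where the SD came from is unknown.

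A reader might also convert the inputs under exponential times: HR = 6.6/10.2, giving 4 × 3.24² / (ln HR)² = 222 events, more than the 172 participants. That model forces an SD of 10.2 in the active arm, against the protocol's single SD of 6.6, so no conclusion is drawn from it.

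**Conclusion.** The point holds and should be settled before unblinding. Three things rest on the text and arithmetic alone: the outcome is right-censored at week 60 or at drop-out, no rule covers participants without an addition, and the sample size treats the time as fully observed. The planning SD cannot arise over 48 weeks and could arise by week 60 only in a near-degenerate pattern, so the 90% power is not a statement about this trial.

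The size of the loss depends on assumptions. Under the Weibull scenarios, leaving out non-adders takes t-test power to between 80% and 7%, where log-rank has 91% to 63%. Tying them at week 60 costs little power but changes what is estimated. These scenarios ignore drop-out and rest on an assumed control mean. Whether the trial is underpowered for a log-rank test cannot be decided from the documents, because they give no event proportion or hazard ratio.

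**What to change.** In Statistical methods, name the mild-unit primary analysis:

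- outcome: time from randomisation to the first start or increase of levodopa, following the event as the Mild PD section describes it;
- participants without an event censored at week 60 or at last contact;
- log-rank test and Cox model, both stratified by centre, which is the randomisation stratum;
- Kaplan–Meier curves, and a restricted mean difference at the same week 60 horizon to keep a scale in months.

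In Sample size, replace the 3.6/6.6-month power statement with the power at the existing 172 participants over a stated range of control event proportions and hazard ratios. A single figure would need an event rate that the protocol does not give.

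The cost is wording in the protocol or analysis plan. The date of addition is already recorded, and no visit or recruitment target changes. The downside is that the restated power may fall below 90%.

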### Randomization

Stratified group randomization will be applied in this study. Allocation will be applied by block randomization stratified by study centre with block sizes of 4 using SPSS 25.0 software, and the subjects will be randomly divided into the intervention group or control group (Seed Number: 202106151) in a 1:1 ratio. The randomization sequence will be kept in sealed opaque envelopes and will be prepared and preserved by the pharmaceutical company. Researchers in charge of enrolment and evaluation will be blinded to the patient allocation. After the participants are enrolled, they will be given an enrolment number by the sequence they take part in the study, and then they will be given the investigational medicinal product (IMP). An emergency unblinding envelope will be set for each blind code, indicating to which group the subject is assigned and what medication intervention the participant is receiving. Those sealed opaque envelopes will be sent to each study centre together with the study medications of the corresponding blinding code. Each centre will assign a research assistant responsible for allocating the drugs to the participants, and emergency unblinding envelopes will be kept by them.

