### Eligibility criteria

Participants must fulfil the diagnostic criteria of clinically probable PD according to the 2015 Movement Disorder Society (MDS) criteria. Patients will be screened according to the inclusion and exclusion criteria listed in Table 1. Patients of all stages are allowed to take anti-Parkinson treatment given by neurological physicians according to guidelines. The treatment should be at a relatively stable dosage for at least 3 months prior to the intervention, and their clinical features should also be relatively stable; thus, no plan should be made to change their existing treatment during follow-up.

**Table 1 Tab1:** Eligibility criteria

Inclusion criteria	
Age between 30 and 80, regardless of gender	
For participants who are receiving anti-Parkinson treatment (levodopa preparations, dopamine agonists, monoamine oxidase inhibitors, catechins-o-methyl transferase (COMT) inhibitor, anticholinergic drugs, etc.), the dosage of the anti-Parkinson drug is requested to be relatively stable for at least 3 months before this clinical trial, and no plan has been made to change the existing treatment in the next 3 months	
Voluntarily participate and sign informed consent	
Exclusion criteria	
Patients with Parkinson Syndrome (PS) or Parkinsonism-Plus syndrome (PPS)	
Pregnant or lactating women, history of drug or alcohol abuse	
Severe cognitive impairment (Montreal Cognitive Assessment scale (MoCA) < 20 points), active depression or psychosis and/or under antidepressant or antipsychotic medication, severe sequelae of stroke and other systemic diseases affecting the heart, lung, liver or kidney	
Participating in other clinical studies or have participated in other clinical study within the previous 30 days	

Grouping will be conducted according to the Hoehn & Yahr stage at baseline. Stage ≤ 2 will be classified into the mild PD group, stage 2.5 and 3 into the moderate group, and stage ≥ 4 into the advanced group [7]. For patients in the moderate group, at least one of the following motor complications should be reported: wearing-off phenomenon, peak-dose dyskinesia, biphasic dyskinesia, dysmyotonia, and on–off phenomenon. No extra TCM syndrome differentiation will be applied since the correspondence between the TCM syndrome and clinical stage has been described above.

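### Mild unit: the primary event includes a levodopa increase but fixes no reference dose, so restoring a reduced entry dose can count as progression; the stated comparison also leaves out baseline levodopa use

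*Protocol article*

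**What the plan says.** The Outcomes section for mild PD makes the time of first addition of levodopa the primary outcome, as a marker of progression. It sets a gate, "When participants have a 3-point-higher UPDRS III score and have more serious symptoms", and says that physicians may then act: "their physicians could give them levodopa or increase the dose of levodopa they were taking". The timing is recorded. The event therefore covers both a levodopa start and a dose increase.

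Both kinds of patient can enter. Table 1 under Eligibility criteria sets a stable-dose condition, "For participants who are receiving anti-Parkinson treatment (levodopa preparations, dopamine agonists" and other classes, and does not restrict levodopa use in the mild unit. Under Therapy combination, untreated patients postpone Western medicine, while treated patients "should continue to take them on the basis of the original dosage". The same section adds: "Reduction of the dosage of anti-Parkinson medication is allowed due to the variations of the disease condition".

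Therapy combination ties the score part of the gate to entry: the UPDRS "total score is 3 points higher than at baseline". It does not tie the dose to entry in the same way. It does require that "the time of adjustment and the current dose should be recorded in detail in the CRF".

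On the analysis, the Randomization section says: "Allocation will be applied by block randomization stratified by study centre with block sizes of 4". Statistical methods gives a t-test or Mann-Whitney U test for two-group comparisons. It mentions ANOVA or GEE for multivariate analysis and names no factors.

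**The concern.** Combining a start and an increase into one event, read as a need for more levodopa, is a reasonable choice. The weak spot is the meaning of an increase. If the reference is the dose at the time, a patient who only recovers a reduced dose has an event. If the reference is the entry dose, that patient has none. The text allows either reading. The outcome is meant to show progression, and a return to the entry dose does not show that more levodopa is needed than at entry.

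A second, smaller matter follows from the same definition. Levodopa use at entry decides which event a participant can have: a start in non-users, an increase in users. The two event types may differ in typical timing. The stated two-group test ignores a factor that is known at entry and may explain part of the spread.

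**Working it through.** **1. The route to a counted return, step by step**

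- Entry: a levodopa user is on a stable dose D, and the baseline UPDRS is scored on D.
- During the trial the dose is reduced to below D, which Therapy combination allows.
- Later the score is 3 points above baseline and symptoms are worse, so the gate is met. This score is taken on less than D.
- The physician returns the dose to D. Against the dose at the time, this is an increase; against the entry dose, it is not.

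The gate does not close this route. The baseline score belongs to D and the later score to a lower dose, so part or all of a 3-point rise may come from the reduction itself.

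**2. What one counted return would do**

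Inputs: 60 weeks of observation (Study setting: 48 weeks of therapy plus 12 of follow-up), and 72 per group with a planned difference of 3.6 months (Sample size). Assumption not in the document: a participant without an event is given week 60.

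- Week 60 = 420/30.44 = 13.80 months; week 12 = 84/30.44 = 2.76; week 48 = 336/30.44 = 11.04.
- Return counted at week 12: (13.80 - 2.76)/72 = 0.153 months; 0.153/3.6 = 4.3%.
- Return counted at week 48: (13.80 - 11.04)/72 = 0.038 months; 0.038/3.6 = 1.1%.

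These are effects of a single participant on one arm's mean. The document gives no rate of reductions or returns, so no total can be computed.

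**3. Baseline levodopa use: precision**

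The plan's own figure first:

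- n = 2 x [(1.96 + 1.28) x 6.6/3.6]^2 + 0.25 x 1.96^2 = 2 x 5.94^2 + 0.96 = 71.5, so 72 per group. This reproduces the stated 72.

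Now take 6.6 as the pooled S.D. over users and non-users. Let p be the share on levodopa at entry and g the difference in mean time between the two event types. Neither is given; assume p = 20% to 60% and g = 3 months. Adjustment removes the between-type part: S.D. = sqrt(6.6^2 - p(1 - p)g^2).

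| p | p(1 - p)g^2 | adjusted S.D. | n by the plan's formula |
|---|---|---|---|
| 0.2 | 1.44 | 6.49 | 69.2, so 70 |
| 0.5 | 2.25 | 6.43 | 67.9, so 68 |
| 0.6 | 2.16 | 6.43 | 68.03, so 69 |

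On these assumptions, adjustment saves 2 to 4 participants per group.

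**The case against.** **The quoted sentence is a treatment permission and may already mean the entry dose.** It says what physicians may do. With the outcome called an addition and treated patients kept on their original dosage, levodopa on top of the entry regimen is a natural reading. This stands in part. A reader might infer that the protocol measures an increase against the current dose and excludes the entry dose; the text does not say that. It leaves the reference open. But the same paragraph goes on to record the timing as the outcome, so the permission also works as the event description, and the choice matters.

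**A journal article need not carry edge-case rules.** This has some force. The point is kept because the article itself describes the event, and physicians and adjudicators apply it while the trial runs.

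**The route is narrow, and safeguards exist.** It needs a user on a stable dose, then a reduction, then the gate, then a return to the entry dose. Doses go into the CRF, and Data management names an endpoint adjudicator. All true, and it is why the point is minor. The records let a return be found, but the article gives the adjudicator no rule on whether it counts.

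**Covariates are commonly left to an analysis plan, and randomization keeps the unadjusted test valid.** Both stand. Stratifying by centre alone is also a legitimate choice. What remains is a cheap improvement.

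**A stronger reading on power.** A reader might infer that ignoring baseline levodopa use leaves the mild unit underpowered, by taking 6.6 as the S.D. within each event type and adding the between-type spread. With the same p and g, that gives a pooled S.D. of 6.71 to 6.77. The documents do not support it. If times lie within 60 weeks, no S.D. can exceed 13.80/2 = 6.90, and with arm means 3.6 months apart the within-arm S.D. cannot exceed sqrt(6.90^2 - 1.8^2) = 6.66. The inflated values lie above that limit.

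**Conclusion.** The concern holds as a minor one. The mild unit's primary event includes a levodopa increase without a fixed reference dose. Because reductions are allowed, a gated return to the entry dose can be counted as progression.

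Its size cannot be established. Each such event would move an arm mean by roughly 0.04 to 0.15 months under the week-60 assumption, and the number of such events is unknown. A reader might infer a bias for or against the formula. The documents give no basis for that: they do not show that reductions or returns would be more common in one arm.

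The stated comparison also makes no use of levodopa status at entry. Including it is a small gain, about 68-70 instead of 72 per group. This holds if 6.6 is the pooled S.D., 20-60% are on levodopa and the event types differ by 3 months, all of which are assumed. The unadjusted test is not wrong.

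**What to change.** Keep the existing worsening gate and define the event as:

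- in participants not on levodopa at entry, the first levodopa start;
- in participants on levodopa at entry, the first levodopa dose above their own entry dose.

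State that a return to the entry dose after a reduction is not an event.

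In the primary analysis, adjust for levodopa use at entry (on versus not on), for example in the ANOVA-type model that Statistical methods already allows, in place of the unadjusted two-group test. The randomization need not change.

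The cost is one or two sentences in the outcome definition and one analysis factor. No new data are needed: adjustment times and doses already go into the CRF, and baseline use is known at entry. The rule can be fixed before unblinding. The downside is slightly fewer counted events and one more term in the model.

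### The mild-unit primary event appears to be a levodopa start for some participants and a dose increase for others; define it so and adjust for baseline levodopa use (minor)

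*Protocol article*

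**What the plan says.** All references are to the protocol article.

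- **Outcomes, Mild PD.** The primary outcome is when levodopa is first added. Once the UPDRS III score has risen by 3 points and symptoms are worse, "their physicians could give them levodopa or increase the dose of levodopa they were taking". The timing is then recorded.
- **Eligibility criteria.** The mild unit is defined by Hoehn & Yahr stage 2 or below. "Patients of all stages are allowed to take anti-Parkinson treatment given by neurological physicians according to guidelines", and Table 1 lists levodopa preparations among those treatments.
- **Therapy combination.** Participants who have taken no anti-Parkinson drug "should postpone the application of Western medicine and take IMPs". For the rest: "Patients who have already received anti-Parkinson treatment should continue to take them on the basis of the original dosage".
- **Randomization.** "Allocation will be applied by block randomization stratified by study centre with block sizes of 4". Baseline treatment is not a stratum.
- **Sample size.** The outcome is planned as a difference in means: "the estimated difference in the time of first addition of levodopa between the two groups among mild PD patients was 3.6 months", with SD 6.6.
- **Statistical methods.** "Comparisons between two groups will be conducted using Student’s t-test or the Mann–Whitney U test". ANOVA or GEE is also named for multivariate analysis, but with no covariates and no link to this outcome.

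**The concern.** A participant already on levodopa cannot have levodopa added for the first time. For that person the event can only be a dose increase, whereas for everyone else it is a start. One label therefore seems to cover two clinical events, and which one applies is fixed by treatment at baseline.

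Two things are at stake, both modest. The first is clarity: the outcome's name does not describe what is counted in levodopa users. The second is precision: if levodopa users reach their event sooner or later than others, that spread stays in the error term of an unadjusted test, and the interval is wider than it need be.

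**Working it through.** **1. Reproduce the plan.** Inputs from Sample size: difference 3.6 months, SD 6.6, normal quantiles 1.96 and 1.28.

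- n per group = 2 × [(1.96 + 1.28) × 6.6 / 3.6]² + 1.96²/4 = 2 × 5.94² + 0.96 = 71.5, so 72. This is the stated figure.
- Power at 72 per group = Φ(3.6 / (6.6 × √(2/72)) − 1.96) = Φ(3.27 − 1.96) = 90.5%.

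**2. Does the mixed unit harm the unadjusted test?** Simulation of a t-test with 72 per group, total SD 6.6 and 20,000 runs, with assumed mixes:

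- Half on levodopa, mean gap 6.6 months: type I error 5.1%, power 90.5%.
- 30% on levodopa, gap 5 months: type I error 5.0%, power 90.1%.

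So the test holds its level and its planned power. This takes 6.6 as the total SD; if it came from a similar mix of patients, it already contains the spread between users and non-users.

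**3. What adjustment could add, with fully observed times.** Let q be the share on levodopa at baseline and D the gap in mean time between users and the rest. Neither is in the article; both are assumed. Adjusted SD = √(6.6² − q(1 − q)D²).

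| D (months) | q | Adjusted SD | Power at 72 per group |
|---|---|---|---|
| 1 | 0.5 | √(43.56 − 0.25) = 6.58 | 90.7% |
| 3 | 0.1 | √(43.56 − 0.81) = 6.54 | 91.0% |
| 3 | 0.5 | √(43.56 − 2.25) = 6.43 | 91.9% |
| 6 | 0.1 | √(43.56 − 3.24) = 6.35 | 92.5% |
| 6 | 0.5 | √(43.56 − 9.00) = 5.88 | 95.7% |

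These figures are indicative only. Follow-up is 48 + 12 = 60 weeks, or 13.8 months, and times confined to 0–13.8 months have an SD of at most 13.8/2 = 6.9. An SD of 6.6 is close to that ceiling, so a normal model with fully observed times fits poorly. D = 6 is an illustration, not a bound.

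**4. The same question with times capped at 13.8 months.** This stays with the kind of analysis the article names: a linear model on the capped times, with and without levodopa yes/no. Assumed: 72 per group, exponential times, 60% events, treatment hazard ratio 0.5, half on levodopa.

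| Background hazard ratio | Unadjusted | Adjusted | Difference (points) |
|---|---|---|---|
| 1 | 83.7% | 83.4% | −0.3 |
| 1.5 | 83.1% | 83.4% | +0.3 |
| 2 | 82.5% | 84.5% | +2.0 |
| 3 | 79.0% | 84.4% | +5.4 |

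Type I error stayed near 5% throughout. The power levels follow from the assumed treatment effect and are not comparable with the planned 90.5%; only the differences within rows matter here.

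**The case against.** The strongest reply is that covariate lists belong in a statistical analysis plan, which is not shown, and that ANOVA or GEE could carry baseline levodopa use. This stands: missing adjustment alone would not be a finding, nor would a missing breakdown of events by type. What remains is the event itself. Its definition is protocol content, and the article gives it a name that does not fit levodopa users.

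A second reply is that the article never says a dose increase counts. It names the outcome and then says what physicians may do. This also stands, so the mixed event is an inference, though the natural one. It does not remove the need for a sentence: if increases do not count, levodopa users have no definable first addition.

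A third reply is that the gain is speculative. It is negligible at background hazard ratios of 1 to 1.5, and the larger figures depend on a share and a gap that nobody has stated. This stands as well.

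A reader might go further and infer that pooling starts with increases biases the comparison, or that the unit is underpowered. The documents support neither. Participants are randomised within centre whatever their baseline drugs, so the comparison of formula with placebo on permitted background treatment is fair, and the planned sample size reproduces.

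**Conclusion.** Minor. On the natural reading, the mild-unit primary event is a levodopa start for some and a dose increase for others, under a label that describes only the first, and the two-group tests named do not account for this. The primary comparison is unbiased, keeps its 5% level and meets its planned power, so nothing in it is wrong.

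The size of the benefit cannot be fixed from the article. Adjustment gains about nothing if baseline levodopa use hardly predicts the time to event, and roughly 2 to 5 power points if the background hazard ratio is 2 to 3 and half the unit is on levodopa. Those inputs, the 60% event proportion and the treatment hazard ratio of 0.5 are assumptions.

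**What to change.** Two changes:

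1. In the Mild PD outcome section, state that the event is the first levodopa start or, for participants on levodopa at baseline, the first increase in levodopa dose.
2. Include baseline levodopa use (yes/no) as a factor in the mild-unit primary analysis, fixed before unblinding.

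Sample size and randomisation stay unchanged. The cost is one degree of freedom and a little extra analysis; in the capped-time check with no background effect, power moved by 0.3 points. Baseline levodopa use is not in the article's list of baseline characteristics, but it has to be known to apply the criterion of a stable dose for three months, so no new visit or measurement should be needed.
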